## Abstract

**Background:**

The Exercise and Nutrition Routine Improving Cancer Health (ENRICH) study is investigating a novel lifestyle intervention aimed at improving the health behaviors of adult cancer survivors and their carers. The main purpose of the study is to determine the efficacy of lifestyle education and skill development delivered via group-based sessions on the physical activity and dietary behaviors of participants. This article describes the intervention development, study design, and participant recruitment.

**Methods/Design:**

ENRICH is a randomized controlled trial, conducted in Australia, with two arms: an intervention group participating in six, two-hour face-to-face sessions held over eight weeks, and a wait-list control group. Intervention sessions are co-facilitated by an exercise physiologist and dietician. Content includes healthy eating education, and a home-based walking (utilizing a pedometer) and resistance training program (utilizing elastic tubing resistance devices). The program was developed with reference to social cognitive theory and chronic disease self-management models. The study population consists of cancer survivors (post active-treatment) and their carers recruited through community-based advertising and referral from health professionals. The primary outcome is seven-days of sealed pedometry. Secondary outcomes include: self-reported physical activity levels, dietary intake, sedentary behavior, waist circumference, body mass index, quality of life, and perceived social support. The outcomes will be measured at baseline (one week prior to attending the program), eight-weeks (at completion of intervention sessions), and 20-weeks. The intervention group will also be invited to complete 12-month follow-up data collection. Process evaluation data will be obtained from participants by questionnaire and attendance records.

**Discussion:**

No trials are yet available that have evaluated the efficacy of group-based lifestyle education and skill development amongst mixed groups of cancer survivors and their carers. The results will have implications for the planning and provision of health and support services during the cancer survivorship phase.

**Clinical Trials Registration:**

Australian New Zealand Clinical Trials Register identifier: ANZCTRN12609001086257.

## Background

The number of cancer survivors worldwide is expected to triple from 25 million in 2008 to 75 million in 2030 [1]. There are approximately 340,000 cancer survivors in Australia, representing about 2% of the Australian population [2]. Cancer survivors are at increased risk of chronic illnesses such as cardiovascular disease and osteoporosis, death from non-cancer causes, cancer recurrence, secondary cancers, as well as long-term and/or late effects of treatment, such as fatigue, depression, pain, reduced quality of life (QoL), and weight loss or gain [3-5]. These increased risks can be attributed to cancer treatment, genetic predisposition, and common lifestyle factors [6].

The role of lifestyle factors such as nutrition, physical activity (PA) and a healthy weight aimed at preventing recurrence, secondary cancers, and other chronic diseases is an emerging area of research [7,8]. The benefits of PA for people affected by cancer include improved cardiovascular fitness, modest improvements in reducing fatigue, and improved mood and quality of life, body composition, sleep, self-esteem, depression, anxiety, and tiredness [9,10]. In breast and bowel cancer survivors, PA is associated with lower risk of disease recurrence and longer survival [11-13]. Resistance training can be safely performed [14], and has been associated with improvements to self esteem, muscular strength, and lean body mass [15]. Evidence is emerging that the pattern of activity is important, with unique metabolic consequences associated with prolonged sedentary behavior [16]. There is a dose-response association between sitting time and mortality from all causes, that is independent of leisure time activity [17], and is associated with the development of bowel, endometrial, ovarian, and prostate cancer, and cancer-specific mortality in women [18].

Diet quality after a breast cancer diagnosis is directly associated with subsequent mental and physical functioning [19,20]. Dietary fat reduction and modest weight loss has also been associated with relapse-free survival in post-menopausal breast cancer patients [21]. Both diet and PA contribute to the development of obesity, itself an independent contributor to risk of cancer recurrence and survival [7,22]. Evidence suggests that making changes in health behaviors (healthy diet and PA) after a cancer diagnosis may have a significant impact on health [23].

This increasing importance of nutrition and PA for cancer survivors, has been recognized in recent guidelines. An international review by the World Cancer Research Fund and American Institute for Cancer Research concluded that cancer survivors should follow the same diet, healthy weight, and physical activity principles for cancer prevention as the general population [7]. These recommendations are: to be as lean as possible within a healthy body weight; be physically active; limit energy dense food and drink; eat mostly foods of plant origin; limit red meat and avoid processed meat; limit salt; and aim to meet nutritional needs through diet alone [6]. The American College of Sports Medicine and Exercise and Sports Science Australia both acknowledge the safety and efficacy of exercise training for cancer survivors, with general recommendations of low to moderate intensity, three to five times per week, and involving aerobic, resistance, or mixed exercise types [14,24].

Despite these lifestyle recommendations from key agencies and professional organizations, cancer survivors' lifestyle behaviors are similar to the general population. An Australian study of cancer survivors found that unhealthy behaviors (physical inactivity, low fruit and vegetable consumption, overweight/obesity, high alcohol consumption) were similar, if not worse, than a matched sample of persons without a cancer history and survivors were also more likely to report a range of chronic co-morbid conditions [25]. Cancer survivors report being interested in lifestyle behaviors, with some evidence suggesting that a cancer diagnosis may provide a 'teachable moment' to improve health [26].

Little is known about the lifestyle behaviors of the carers of cancer survivors. An Australian study reported that for people with a friend or relative diagnosed with cancer, the diagnosis may have been a cue to make positive diet improvements and increase PA [27]. However, research suggests no difference between carers and non-carers on fruit and vegetable consumption, smoking status, alcohol consumption, PA, healthy body weight, or number or type of chronic illness [28,29]. Carers are likely to share many of the same behavioral risk factors as cancer survivors, and would benefit from improvements. Social support appears beneficial in helping cancer survivors make positive changes to exercise behavior [23]. Involving family members in health behavior interventions has positive effects on the patient's adherence to rehabilitation programs, and improved diet and PA behaviors [30,31].

Despite the growing evidence of the benefits and efficacy of lifestyle behaviors in promoting good health and recovery for cancer survivors, there are few services outside of the clinical setting specifically targeting cancer survivors to improve their health. Cancer survivors often report a sense of loss, and feeling "abandoned" or "cast adrift" by the health care system at the time of treatment completion [32]. There is a need to improve support and health services to assist those affected by cancer in the transition from patient to survivor. The main purpose of the present study is to evaluate the acceptability and efficacy of a healthy lifestyle (PA and diet) intervention for cancer survivors and their carers.

## Methods

### Study design

The study utilizes a two-arm randomized controlled trial design with a wait-list control group. Participants complete data collection at baseline, eight and 20 weeks. Intervention participants also complete these measures again at 12 months from baseline. The intervention consists of six, two-hour face-to-face group sessions held over eight weeks. Control group participants are invited to attend ENRICH after completion of the baseline, eight, and 20 week measures. Ethics approval was obtained from the University of Newcastle Human Research Ethics Committee (H-2009-0347). The design, conduct and reporting of this study will adhere to the Consolidated Standards of Reporting Trials (CONSORT) guidelines [33].

### Setting

Three intervention programs and three control programs have been conducted in Sydney, New South Wales, Australia. A further four to six programs are planned to occur in 2011.

### Participants

#### Selection criteria (eligibility)

Participation in the program is open to cancer survivors with a previous diagnosis of any type or stage of cancer and who had completed all active treatment (surgery, chemotherapy, radiotherapy, immunotherapy, bone marrow transplants, etc), and who do not have any food restrictions as a result of surgery or treatment, and to carers of cancer survivors. The inclusion criteria of the study are: 1) cancer survivor or carer of cancer survivor; 2) aged 18 years or older; 3) fluent in English; 4) signed medical clearance from their General Practitioner, and 5) with a functional performance score of two or less on the Eastern Cooperative Oncology Group criteria (that is "at least ambulatory and capable of all self-care but unable to carry out any work activities or up and about more than 50% of waking hours") [34]. Both cancer survivors and carers need to meet eligibility criteria. Survivors and carers may participate independently (that is, the survivor does not need a carer to participate and vice versa) or together. A survivor may also bring more than one carer.

#### Recruitment

Participants are recruited via multiple methods, including referrals from health professionals, medical centers, professional organizations (such as the Dieticians Association of Australia, New South Wales Oncology Groups), community health centers, cancer support groups, local media, and various Cancer Council NSW resources (website, mailing lists, and publications).

### Randomization

Stratified randomization by age group (less than 50, 50-65, older than 65) and gender is used with a block size of four. A random number sequence for each strata is generated using a random function in SAS version 9.2 and generated a random sequence of A and B's to indicate allocation to intervention or control groups.

The Project Co-ordinator uses a random number table to allocate consenting participants to intervention or control group, stratified by age and gender. If a participant has a partner or carer also consenting, they will be randomized together to the same group, stratified by age and gender of the cancer survivor. The Project Co-ordinator is not blinded to group allocation and participant blinding is not possible due to the wait-list control design of the trial.

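### An unblinded co-ordinator allocates from a table with a fixed block of four, so up to about one third of assignments may be deducible in advance

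*Protocol article*

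**What the plan says.** The Randomization section of the protocol article has two paragraphs. The first sets the scheme: "Stratified randomization by age group (less than 50, 50-65, older than 65) and gender is used with a block size of four". On generation it says "A random number sequence for each strata is generated using a random function in SAS version 9.2", and that this "generated a random sequence of A and B's to indicate allocation to intervention or control groups".

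The second paragraph describes how the scheme is carried out: "The Project Co-ordinator uses a random number table to allocate consenting participants to intervention or control group, stratified by age and gender". A consenting partner or carer is randomized with the survivor to the same group, using the survivor's stratum. The section closes: "The Project Co-ordinator is not blinded to group allocation and participant blinding is not possible due to the wait-list control design of the trial".

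Three other places bear on the point. Under Selection criteria (eligibility), "A survivor may also bring more than one carer". Under Procedure, the same co-ordinator makes the reminder calls and keeps the attendance records. Under Setting, three intervention and three control programs have been run, and four to six more are planned.

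**The concern.** Three stated features combine: one fixed block size, an allocator who knows all past assignments, and a table from which that allocator works. In a fixed block, past assignments reveal part of what comes next. If whoever knows the next assignment can also influence who enters, or when, the arms can differ at baseline in ways that no analysis fully removes.

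This trial would be sensitive to such a difference. Treatment is open, the control is a wait-list, and the primary outcome is daily step count, which plausibly depends on motivation. A few keener survivors or carers steered towards the intervention arm would move the main comparison in its favour.

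**Working it through.** **Inputs.** From Randomization: block size 4, the same throughout; 3 age groups × 2 genders = 6 strata. From Statistical power and sample size: a target of 75 per group, so 2 × 75 = 150 participants. The article gives no predictability figure to reproduce. Its sample size is not in question: 2000 steps, SD 3200, 80% power and two-sided 5% (sidedness assumed) give 41.17 per group by the t-test, which rounds up to the stated 42.

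**Assumptions.** The table is the blocked SAS list, and the observer knows the block size and every earlier assignment in the stratum.

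**Certain assignments.** A balanced block of four has 4!/(2!·2!) = 6 equally likely sequences, hence 6 × 4 = 24 positions.
- Positions 1 and 2 are never certain.
- Position 3 is certain when the first two agree (AABB, BBAA): 2 of 6.
- Position 4 is always certain: 6 of 6.
- Total: (0 + 0 + 2 + 6)/24 = 8/24 = 33.3%.

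**Best guess.** Guess the arm that is behind in the block; toss a coin when the arms are level.
- Position 1: 6 × ½ = 3 correct.
- Position 2: the second letter differs from the first in 4 of 6, so 4 correct.
- Position 3: 2 certain, plus 4 × ½ = 2, so 4 correct.
- Position 4: 6 correct.
- Total: (3 + 4 + 4 + 6)/24 = 17/24 = 70.8%, against 50% under full concealment.

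**Scale.** With 150 separate assignments, 150 × 1/3 = 50 would be deducible. This is an upper bound. Survivors and carers share one assignment, so there are fewer than 150, and incomplete final blocks in the six strata contain fewer certain positions.

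**Reading ahead.** If the allocator can see the list before committing a participant, 100% are known, whatever the block size.

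**Effect of varying the block size.** This was simulated as one sequence of 150, repeated 400 times, for an observer who knows the possible sizes but not the size of each block:

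| Blocks | Certain | Best guess right |
|---|---|---|
| 4 only (exact, complete blocks) | 33.3% | 70.8% |
| 4 and 6 | 5.4% | 69.2% |
| 2, 4 and 6 | 4.3% | 70.2% |
| 4, 6 and 8 | 2.2% | 68.0% |

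Varied blocks remove most of the certainty but hardly change guessing accuracy, and they give no protection against reading ahead. Who holds the list matters more than the block size.

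**The case against.** The strongest reply is that an unblinded allocator is not the same as failed concealment. The article does not say that the co-ordinator sees the next assignment. Details of concealment are commonly left to a full protocol, which is not shown here. Nor is the co-ordinator given any part in screening or enrolment: recruitment is by referral, media and mailing lists, entry needs a General Practitioner's clearance, and the reminder calls and attendance records come after entry. All of this stands, and it is why bias is possible and not demonstrated. It does not dispose of the point, because the section states who allocates, from what, with which block size and with what knowledge. The finding rests on that stated procedure and not on an omission.

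A reader might infer three stronger things that the documents do not support.

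- **Two conflicting mechanisms.** The table is said to be used within age and gender strata, so its most natural reading is the stratified SAS list in tabular form. The wording is unclear, but a contradiction is not shown. If a separate, unblocked table was in fact used, the block-of-four figures would not apply, and the stated blocking would not be what was carried out.
- **All upcoming assignments are predictable.** Certainty reaches at most about one third unless the list can be read ahead, and the article does not say that it can.
- **Carers may join once the arm is known.** The eligibility section leaves the number of carers open, but Randomization has the consenting carer randomized together with the survivor. Nothing describes carers joining after disclosure.

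**Conclusion.** The point holds in a limited form. Followed as written, the procedure leaves up to one third of assignments deducible with certainty and a best guess right about 71% of the time. All assignments are known if the list can be read ahead. These figures assume that the table is the blocked SAS list and that the allocator tracks each stratum. Selection bias also requires that the allocator, or someone the allocator informs, can affect who enters or when; the article is silent on this. No effect on step counts can be estimated from the document, and the sample size is unaffected. It is an inexpensive improvement for the remaining programs, and not evidence that the completed ones are biased.

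**What to change.** For the remaining programs:

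1. **Separate the list from recruitment.** The person who generates the SAS sequence, or another existing team member outside recruitment, holds it. That person releases one assignment at a time, after eligibility and the consents of the survivor and any participating carers are logged. This is the essential step.
2. **Vary the block size at random and do not disclose the sizes.** This is secondary: it mainly reduces certain prediction.
3. **Clarify the text.** State whether the random number table is the SAS sequence, who holds it, and what was used for the programs already run.

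The cost is a short procedural amendment with existing staff, a short wait for each assignment, and slightly looser balance within strata. Outcomes, sample size and the intervention do not change. The change cannot protect allocations already made, so the third step matters for how those are reported.

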### Statistical power and sample size

To detect a mean difference of 2000 steps per day in pedometer-derived step counts between the intervention and control groups with 80% power and 5% significance, assuming a standard deviation of 3200 steps, requires 42 subjects per group. The effect size estimate of 2000 steps per day change as the primary outcome is based on published research and clinically meaningful difference [35]. To ensure adequate sample size for secondary outcomes and to account for attrition and missing data, we aim to recruit 75 subjects per group.

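### The 42 per group is the size for independent participants; it makes no allowance for the survivor–carer and group clustering in the design, so the stated 80% power at 42 has almost no slack

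*Protocol article*

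**What the plan says.** All references are to the protocol article.

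- **Statistical power and sample size.** The calculation aims "To detect a mean difference of 2000 steps per day in pedometer-derived step counts between the intervention and control groups". Power is set at 80% and the significance level at 5%. The result is stated as: "assuming a standard deviation of 3200 steps, requires 42 subjects per group". The recruitment target follows: "To ensure adequate sample size for secondary outcomes and to account for attrition and missing data, we aim to recruit 75 subjects per group". No intraclass correlation, design effect or attrition rate is given.
- **Randomization.** "If a participant has a partner or carer also consenting, they will be randomized together to the same group". The stratum is then that of the survivor.
- **Selection criteria (eligibility).** Survivors and carers may also enter on their own. At the other end, "A survivor may also bring more than one carer".
- **Study design.** The intervention is six group sessions over eight weeks. Controls are offered the program only after their 20-week measures.
- **Statistical methods.** Longitudinal data go into GEE models, and the analysis is to allow for clustering within dyads. Clustering by program group is not mentioned.

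**The concern.** The sample size and the analysis rest on different assumptions. The sample size treats every participant as an independent observation. The randomization makes a survivor and any carers one unit, and the analysis section expects their outcomes to be correlated. Group delivery can add correlation in the intervention arm during the comparison period.

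The practical stake is the retention margin. Someone who takes 42 as the number needed would conclude that 75 recruits leave room to lose 33 of 75, or 44%. The margin from 42 to 75 is already assigned to secondary outcomes, attrition and missing data. If clustering also draws on it, the loss that the primary comparison can absorb is smaller than it appears.

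**Working it through.** **Inputs from the protocol article:** difference 2000, SD 3200, power 80%, significance 5%, equal groups. Sidedness is not stated; two-sided is taken, because a one-sided test gives 32.

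**Reproducing 42.** Standardised difference = 2000/3200 = 0.625.

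- Normal approximation: n = 2 × ((1.960 + 0.842)/0.625)² = 40.19, so 41.
- Two-sample t-test: n = 41.17, so 42. Power is 79.8% at 41 and 80.8% at 42.

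The four inputs fully account for 42, so no design effect is hidden in it.

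**Slack.** The design effect (DE) at which 42 falls to 80% power is 42/41.17 = 1.02 (t) or 42/40.19 = 1.045 (normal).

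**Pairs only.** DE = 1 + f × ICC, where f is the share of participants in pairs. Both values are assumptions.

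| f | pair ICC | DE | power at 42, normal (t) | n needed, 41.17 × DE |
|---|---|---|---|---|
| 0.25 | 0.1 | 1.025 | 80.8% (79.8%) | 42.2, so 43 |
| 0.5 | 0.2 | 1.10 | 78.0% (76.9%) | 45.3, so 46 |
| 0.5 | 0.3 | 1.15 | 76.1% (75.0%) | 47.3, so 48 |
| 0.5 | 0.4 | 1.20 | 74.4% (73.2%) | 49.4, so 50 |

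**Pairs plus program groups.** The second term applies to the intervention arm only, so it is halved when averaged over the arms: DE = 1 + f × ICC_pair + ½ × (m − 1) × ICC_group, with m = n/g participants per intervention group. The Setting section reports three intervention programs already run and four to six further programs planned; if these split evenly between arms, g is 5 or 6. With f = 0.5 and ICC_pair = 0.3, setting n = 41.17 × DE gives

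n = 41.17 × (1.15 − ½ ICC_group) / (1 − 41.17 × ½ ICC_group / g).

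| assumed ICC_group | n, 6 groups | n, 5 groups | loss that 75 absorbs |
|---|---|---|---|
| 0.02 | 50.4, so 51 | 51.1, so 52 | 31–32% |
| 0.05 | 55.9, so 56 | 58.3, so 59 | 21–25% |
| 0.10 | 68.9, so 69 | 77.0, so 77 | 8% to none |

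**What 75 absorbs.** With no loss, a total DE of 75/42 = 1.79. With an assumed 20% loss, 60 are analysed and the limit is 60/42 = 1.43.

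**The case against.** **The number itself is not wrong.** It reproduces exactly. The fault is an omitted design assumption, not a slip in calculation. This stands.

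**The shortfall cannot be sized from the documents.** They give no ICC, no paired share and no group size, and participants may enter singly. In the mildest case above, power at 42 is 79.8–80.8%, in effect the stated figure. Most of the larger increases come from the program-group ICC, which is the least supported assumption: the walking and resistance programs are home-based, and the analysis section anticipates only dyad clustering. This stands, and it is why only ranges are given.

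**Baseline adjustment could offset the loss.** If SD 3200 is cross-sectional and the model uses baseline step counts, variance falls by about 1 − r², where r is the baseline correlation. With an assumed r = 0.5, a design effect of 1.385 becomes 1.385 × 0.75 = 1.04, and power at 42 is about 80%. With r = 0.3, power is about 82% at a design effect of 1.10 but 77% at 1.25. If 3200 is already the SD of change, the offset largely disappears. The article does not say which SD it is. The point stands as a possibility, so it cannot be said flatly that 42 fails.

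**Enrolment is 75, not 42.** A reader might infer that the trial is underpowered. The documents do not support that, because the margin to 75 covers a substantial design effect. Nor does the article claim a 44% attrition allowance; that is only the ratio of its two numbers. What remains is that the article states a requirement that its own randomization and analysis sections do not match.

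**Conclusion.** The point holds in a limited form. The 42 per group is correct for independent participants only, and the article describes a design in which many may not be independent. Any non-trivial positive clustering takes 42 below the stated 80%, unless a baseline-adjusted analysis makes up the difference.

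The size is conditional. Pair clustering alone, at the assumed half paired and ICC 0.2–0.4, costs a few percentage points of power and raises the need to 46–50 analysed per group. An assumed program-group ICC of 0.02–0.10 on top (pair ICC 0.3, five or six groups) raises it to about 51–77 on the t-test base. None of these is an estimate for this trial, and no single replacement figure is established.

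The trial at 75 per group is not shown to be underpowered. It absorbs a total design effect of about 1.8 with no loss, or about 1.4 with an assumed 20% loss. The correction is worth making because the stated requirement governs how much attrition the team thinks it can accept, and further programs are still planned.

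**What to change.** Keep the target of 75 per group and revise the sample size paragraph:

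1. Label 42 as the number needed if participants were independent, and say whether SD 3200 is of change or cross-sectional.
2. Apply a design effect for survivor–carer units and for program groups in the intervention arm. Take the paired share and group sizes from the programs already run, and state the ICC assumptions with a range.
3. Restate the number of analysed participants per group needed for 80% power, using one method throughout (t-test or normal approximation).
4. State the loss that 75 can then absorb, and keep secondary outcomes as a separate reason for the margin.

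The illustrative values above should not be written in as the answer. The cost is wording and a short calculation from existing records, with no extra participants. The only downside is a less favourable stated requirement and margin.
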